## Abstract

**Background:**

Human immunodeficiency virus (HIV)-related chronic lung disease (CLD) among children is associated with substantial morbidity, despite antiretroviral therapy. This may be a consequence of repeated respiratory tract infections and/or dysregulated immune activation that accompanies HIV infection. Macrolides have anti-inflammatory and antimicrobial properties, and we hypothesised that azithromycin would reduce decline in lung function and morbidity through preventing respiratory tract infections and controlling systemic inflammation.

**Methods/design:**

We are conducting a multicentre (Malawi and Zimbabwe), double-blind, randomised controlled trial of a 12-month course of weekly azithromycin versus placebo. The primary outcome is the mean change in forced expiratory volume in 1 second (FEV_1_) z-score at 12 months. Participants are followed up to 18 months to explore the durability of effect. Secondary outcomes are FEV_1_ z-score at 18 months, time to death, time to first acute respiratory exacerbation, number of exacerbations, number of hospitalisations, weight for age z-score at 12 and 18 months, number of adverse events, number of malaria episodes, number of bloodstream *Salmonella* typhi infections and number of gastroenteritis episodes. Participants will be followed up 3-monthly, and lung function will be assessed every 6 months. Laboratory substudies will be done to investigate the impact of azithromycin on systemic inflammation and on development of antimicrobial resistance as well as impact on the nasopharyngeal, lung and gut microbiome.

**Discussion:**

The results of this trial will be of clinical relevance because there are no established guidelines on the treatment and management of HIV-associated CLD in children in sub-Saharan Africa, where 80% of the world’s HIV-infected children live and where HIV-associated CLD is highly prevalent.

**Trial registration:**

ClinicalTrials.gov, NCT02426112. Registered on 21 April 2015.

**Electronic supplementary material:**

The online version of this article (doi:10.1186/s13063-017-2344-2) contains supplementary material, which is available to authorized users.

## Background

Respiratory disease is the most common manifestation of human immunodeficiency virus (HIV)/acquired immunodeficiency syndrome (AIDS) among children in sub-Saharan Africa, accounting for more than 50% of HIV-associated mortality [1–8]. The use of antiretroviral therapy (ART) and co-trimoxazole prophylaxis has contributed to a reduction in the rate of acute respiratory tract infections and mortality among HIV-infected children in both high- and low-resource settings [9].

However, studies in recent years in sub-Saharan Africa have demonstrated that about 30% of perinatally HIV-infected older children and adolescents have chronic respiratory symptoms, including chronic cough, reduced exercise tolerance and significantly impaired lung function [4, 8]. In these studies, even participants with pronounced respiratory impairment looked well at rest, and plain radiological abnormalities were subtle. High-resolution computed tomography findings showed predominantly small airway disease consistent with constrictive obliterative bronchiolitis (OB) [4, 10]. Importantly, no association was observed between abnormal lung function, ART use or duration or CD4 count, suggesting that this form of HIV-related chronic lung disease may not be responsive to ART.

OB is a chronic obstructive lung disease that follows a severe insult to the lower respiratory tract, resulting in fibrosis of the small airways [11]. The most common presentation is the post-infectious variant, closely related to severe viral infection in the first 3 years of life [12]. It is also seen in the context of allogeneic haematopoietic stem cell (HSC) and lung transplant recipients as a result of a graft-versus-host reaction [13, 14]. HIV is associated with both high incidence of respiratory infections and persistent immune activation despite ART [15–17]. Thus, HIV-associated OB may share causal pathways with both post-infectious and post-transplant variants.

Evidence regarding the efficacy of treatment modalities in OB is sparse. Observational studies have shown some improvement of lung function in a small number of children treated with high-dose pulse corticosteroids for post-transplant OB [14, 18]. Studies in lung transplant-associated OB have shown a positive effect of azithromycin, whereas a small randomised controlled trial of patients with established HSC-associated OB failed to show an effect [19, 20]. Authors of case series including patients with post-infectious and post-transplant OB have reported a benefit of azithromycin on lung function and on rate of exacerbations [21].

Azithromycin is a macrolide antibiotic with bacteriostatic activity against the most common respiratory bacterial pathogens. However, it also has a robust immunomodulatory effect resulting in decreased production of pro-inflammatory cytokines in the acute phase and resolution of chronic inflammation in the later phases. Specifically, azithromycin has direct activity on airway epithelial cells to maintain their function and reduce mucus secretion [20, 22–24]. These characteristics have resulted in the use of azithromycin in the management of a variety of chronic lung diseases, including cystic fibrosis [25], non-cystic fibrosis bronchiectasis [26], bronchiolitis obliterans syndrome [19, 27] and chronic obstructive pulmonary disease [28]. The intracellular uptake of azithromycin is high, and hepatic excretion is slow, resulting in a long half-life that enables infrequent dosing. We will test the hypothesis that prophylactic azithromycin is effective, through its antimicrobial and anti-inflammatory properties, in preventing worsening of lung function and in reducing exacerbations in children and adolescents receiving ART who have HIV-associated chronic lung disease.

## Methods/design

### Study design

BREATHE (Bronchopulmonary function in response to azithromycin treatment for chronic lung disease in HIV-infected children) is a two-site, double-blind, placebo-controlled, individually randomised trial in which we intend to enrol 400 perinatally HIV-infected children and adolescents aged 6–19 years with HIV-associated chronic lung disease who have been receiving ART for a minimum of 6 months. Participants will be enrolled from the outpatient HIV clinics in Harare, Zimbabwe, and Blantyre, Malawi.

### Study intervention

Participants are randomly assigned to receive either azithromycin or placebo in a 1:1 ratio. Weight-band azithromycin (10–19.9 kg, 250 mg; 20–29.9 kg, 500 mg; 30–39.9 kg, 750 mg; > 40 kg, 1250 mg/week) or placebo will be given weekly under direct observation by a treatment monitor identified within the family for a total of 12 months.

### Study population

HIV-infected children and adolescents with HIV-associated chronic lung disease attending outpatient HIV clinics in Harare and Blantyre will be enrolled in the trial. Individuals aged 6–19 years will be approached together with their guardians during their routine HIV outpatient visits and provided with information about the study. Once informed consent is obtained for screening, eligibility will be established using a multi-step screening procedure. Chronic lung disease will be established by spirometry (forced expiratory volume in 1 second [FEV_1_] z-score less than −1.0) with no reversibility (< 12% improvement in FEV_1_ after salbutamol 200 μg inhaled using a spacer). Spirometry will be performed using the EasyOne™ spirometer (ndd Medical Technologies Inc., Andover, MA, USA) by trained research staff certified in performing spirometry and following the American Thoracic Society guidelines. Those who meet the criteria for chronic lung disease will undergo further tests, including a urine pregnancy test (for girls who have reached menarche), serum creatinine, alanine aminotransferase (ALT), an electrocardiogram and screening for tuberculosis (TB). For TB screening, we will use the Xpert™ MTB/RIF (Cepheid, Sunnyvale, CA, USA) to test one sputum sample obtained either spontaneously or through induction.

### Inclusion/exclusion criteria

Perinatally HIV-infected children and adolescents aged 6–19 years who have been receiving ART for at least 6 months for HIV-associated chronic lung disease, who have a firm home address and a stable guardian, and with consent from the guardian and assent from the participant (for those aged < 18 years; those aged ≥ 18 years to consent independently) will be eligible for inclusion. Exclusion criteria will include having a condition that may prove fatal during the study period (e.g., malignancy), TB or acute respiratory tract infection at the time of screening, pregnancy or breastfeeding, history of cardiac arrhythmia, a prolonged QTc interval, abnormal creatinine clearance or elevated ALT, known macrolide hypersensitivity, and concomitant use of digoxin and/or fluconazole (or other drugs known to prolong the QTc interval) (Table 1).

### Study procedures

Eligible individuals will be randomised to either azithromycin or placebo. The allocation ratio will be 1:1 by block randomisation with variable-length blocks stratified by site. The randomisation schedule and allocation list will be generated using Stata™ version 14 software (2015 release; StataCorp, College Station, TX, USA) by an independent statistician not connected with the study. The allocation list will be sent directly to the study pharmacists at both trial sites, who will prepare the study medication. Participants and study personnel will therefore be masked to treatment allocation. The pharmacist will be provided with only randomly allocated numbers assigning participants to arm 1 or arm 2, with each number linked to a study number, and therefore the pharmacist will also remain blinded. It will not be possible to have pre-prepared medication packs, owing to changes of dose with weight.

After randomisation, spirometry will be repeated, and cardiopulmonary fitness will be evaluated using the incremental shuttle walk test. Transthoracic echocardiography will be performed by a trained echocardiographer using the SonoSite™ M-Turbo echocardiography system (FUJIFILM SonoSite, Bothell, WA, USA) at the Malawi site and the Mindray™ DC-N6 echocardiography system (Mindray, Shenzhen, China) at the Zimbabwe site to assess right heart function and pulmonary hypertension. The research nurse will take a rectal swab, nasal aspirate, and sputum and blood samples. The blood sample will be used to measure CD4 count with the Pima™ Analyser (Alere, Orlando, FL, USA) and to perform viral load testing (Xpert™ HIV-1 Viral Load; Cepheid). The study drug will be dispensed by the study pharmacist. After the enrolment visit, follow-up visits will be scheduled at 2 weeks and 3-monthly thereafter. Participants will be followed for a minimum of 12 months to ascertain the primary outcome and for a further 6 months (i.e., 6 months following completion of study drug) to investigate durability of effect (if any) of the intervention. Procedures undertaken at the follow-up visits are summarised in Fig. 1.

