### Outcome measures

The primary outcome is the mean difference between trial arms in FEV_1_ z-scores (generated using Global Lung Function Initiative reference standards) between trial arms at 12 months after initiation of the study drug, adjusted for site and baseline FEV_1_ z-score. The secondary outcomes are described in Table 2.

**Table 1 Tab1:** Inclusion/exclusion criteria

Inclusion criteria • Perinatally acquired HIV (self-report of no sexual debut or blood transfusions, a history of orphanhood owing to maternal HIV disease and/or a history of sibling death due to HIV, and characteristic clinical features (i.e., stunting, history of recurrent minor infections in childhood and planar warts) • Aged 6–19 years • On first- or second-line ART for ≥ 6 months • Chronic lung disease (FEV_1_ z-score less than −1 and < 12% improvement with bronchodilator) • Firm home address accessible in Blantyre/Harare and intending to remain there for 18 months • Stable caregiver for participants aged < 18 years • HIV status disclosed to the child (for those aged > 12 years) • Informed consent to participate in the trial (for those aged < 18 years, consent from guardian and assent from participant; for those aged ≥ 18 years, consent from participant)
Exclusion criteria • Any condition that may prove fatal during the study period • Diagnosis of tuberculosis at enrolment • Acute respiratory tract infection during enrolment • Pregnancy and breastfeeding • History of prolonged QTc syndrome or current or planned therapy with drugs likely to cause cardiac dysrhythmias • History of cholestatic jaundice or hepatic dysfunction associated with previous use of azithromycin or known hypersensitivity to a macrolide or ketolide drug • Prolonged QTc interval (> 440 milliseconds in males; > 460 milliseconds in females) • Creatinine clearance < 30 ml/minute • ALT > 80 IU/L • Concomitant use of digoxin and/or fluconazole • Lack of understanding of the study procedure or uncooperative behaviour

*Abbreviations: ALT* Alanine aminotransferase, *ART* Antiretroviral therapy, *FEV*
_*1*_ Forced expiratory volume in 1 second, *HIV* Human immunodeficiency virus

**Table 2 Tab2:** Secondary outcomes

Outcome	Time point
Time to first respiratory exacerbation	
Time to death	
Number of acute exacerbations	By 12 months
Number of hospitalisations	By 12 months
Number of mild, moderate and severe adverse events	By 12 months
Mean weight-for-age z-score adjusted for baseline	By 12 months

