### Data collection and management and analysis plan

Research nurses and assistants collect the data at baseline and follow-up and record it on electronic clinical record forms using Google Nexus™ tablets (Google, Mountain View, CA, USA) running OpenDataKit software. In both countries, data will be uploaded, processed and saved to a Microsoft Access database (Microsoft, Redmond, WA, USA) before being exported to Stata version 14.0 software and merged into a single database backed up on a regular basis. Consistency checks and checks for missing data are performed both at data entry and fortnightly once the database has been merged. Laboratory data will be recorded on paper forms and entered into the database using optical character recognition. Spirometric data will be uploaded directly from the spirometer. Echocardiographic data will be recorded on electronic clinical record forms, and these will be processed and saved to the Microsoft Access database for merging with the main trial database.

The primary analysis will be done on a modified intention-to-treat basis [29]. Secondary analyses will include a per-protocol analysis which will be defined using all adherence data prior to unblinding the study. Continuous outcomes will be compared between treatment groups, adjusting for site and baseline measures of the outcome and using linear regression to estimate the mean difference and corresponding 95% CI. Time-to-event outcomes will be assessed using Cox proportional hazards regression and graphically displayed using Kaplan-Meier estimates. Between-group comparisons of binary outcomes will be analysed with logistic regression to estimate ORs and 95% CIs. Count data (e.g., number of hospitalisations) will be analysed using Poisson regression to estimate incidence rate ratios and 95% CIs. All analyses will be adjusted for site. Pre-specified effect modification analyses will include site and baseline severity of lung disease.

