### Sample size and power

The following assumptions were made to calculate the sample size:Mean FEV_1_ z-score of −2.04 in the control groupPatients randomised in equal proportions to the two regimensUp to 25% of participants unassessable owing to loss to follow-up, death or suboptimal spirometric tracesNo change in FEV_1_ z-score in the control armDifference in the trial arm mean FEV_1_ z-scores ranging from 0.15 to 0.3, an effect assumed to be of clinical relevanceSD ranging from 0.55 to 0.82 to assess the impact of variability on the difference in mean value the study has power to detect

Under these assumptions, a sample size of 400 recruited participants and 300 participants with outcome data (25% unassessable based on previous studies of Zimbabwean children) will enable 80% power to detect a difference in trial arm means ranging between 0.17 and 0.23, an effect size (difference in means/SD) of 0.32 (Fig. 2).

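### Two FEV1 z-scores appear to be taken before dosing, but the primary model names only an unspecified baseline; pre-specifying both would give a modest gain in precision at almost no cost

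*Protocol article*

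**What the plan says.** Under Study population, the screening reading decides eligibility: "Chronic lung disease will be established by spirometry", with FEV1 z-score below -1.0 and less than 12% improvement after salbutamol. Every randomised participant should therefore have a screening FEV1 z-score.

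Under Study procedures, a second reading follows: "After randomisation, spirometry will be repeated, and cardiopulmonary fitness will be evaluated using the incremental shuttle walk test". Echocardiography and sampling come next in that paragraph, and then "The study drug will be dispensed by the study pharmacist". The text fixes the second reading only as after randomisation. That it precedes the first dose is inferred from the order of description.

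Under Outcome measures, the primary comparison at 12 months is "adjusted for site and baseline FEV_1_ z-score". The analysis plan section describes continuous outcomes as compared by "adjusting for site and baseline measures of the outcome and using linear regression". Neither place defines the baseline.

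**The concern.** FEV1 depends on effort, and one reading in a child carries measurement error. A covariate measured with error explains less of the 12-month variance than it could. If two pre-treatment readings exist and only one enters the model, some precision already paid for is left unused.

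The two readings also differ in kind. The screening value is selected by the -1.0 cut and so subject to regression to the mean. The enrolment value is not directly selected, but it is taken after randomisation, so its use as a covariate rests on its preceding the first dose and on masking. The choice of baseline also carries into the 18-month FEV1 outcome and, if severity is defined by FEV1, into the planned effect-modification analysis by baseline severity.

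At stake is a few points of power and a clear definition of the main covariate. The validity of the treatment comparison is not in question.

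**Working it through.** **The plan's own figure.** Sample size and power gives 300 assessable participants (150 per arm), "an effect size (difference in means/SD) of 0.32" and 80% power. Two-sided alpha of 0.05 is assumed, in line with the planned 95% CI.

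- Detectable effect = (1.960 + 0.842) × √(2/150) = 0.3235 SD.
- Power at 0.32 SD is 79.1%, so the stated effect size is reproduced.
- 300/(1 − 0.25) = 400 recruited, also reproduced.

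(With SD 0.55 to 0.82, 0.3235 SD is 0.178 to 0.265 z, which differs from the stated 0.17 to 0.23. That is a separate matter and is not used here.)

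**Gain from a second reading, no selection.** Let r be the correlation of one baseline reading with the 12-month value and rb the correlation between the two baseline readings. Both are assumptions.

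- Residual variance with one reading: 1 − r².
- Residual variance with the mean of two exchangeable readings: 1 − 2r²/(1 + rb).
- Ratio k = second ÷ first.
- Power from an 80% base = Φ(0.3235 × √75 / √k − 1.960).
- Equivalent sample size = 300/k.

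| r | rb | One reading | Two readings | Fall | Power | Equivalent N |
|---|---|---|---|---|---|---|
| 0.6 | 0.95 | 0.640 | 0.631 | 1.4% | 80.6% | 304 |
| 0.7 | 0.90 | 0.510 | 0.484 | 5.1% | 82.0% | 316 |
| 0.7 | 0.85 | 0.510 | 0.470 | 7.8% | 83.1% | 325 |
| 0.8 | 0.95 | 0.360 | 0.344 | 4.6% | 81.8% | 314 |
| 0.8 | 0.85 | 0.360 | 0.308 | 14.4% | 85.7% | 351 |
| 0.8 | 0.80 | 0.360 | 0.289 | 19.8% | 87.8% | 374 |

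The last two rows are near a ceiling. If all readings are equally reliable, the correlation between true values at baseline and 12 months is r/rb: 0.8/0.85 = 0.94 and 0.8/0.80 = 1.0. They need almost perfect stability over a year and should not be used as a central estimate.

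**With selection at -1.0.** Simulation: true z-scores have SD 1.0 in the screened population; each reading adds independent error; the 12-month value adds drift and error; only participants with a screening reading below -1.0 are kept. All values are assumed. The retained mean screening z is -1.86 to -1.98, close to the -2.04 in the sample-size section.

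| Screened mean | Error SD | Drift SD | rb after selection | r after selection | Fall v. enrolment alone | Fall v. screening alone | Power from 80% |
|---|---|---|---|---|---|---|---|
| -1.3 | 0.3 | 0.4 | 0.83 | 0.74 | 10% | 12% | 84.0% |
| -1.3 | 0.4 | 0.4 | 0.74 | 0.68 | 11% | 14% | 84.3% |
| -1.3 | 0.3 | 0.6 | 0.83 | 0.66 | 6% | 7% | 82.5% |
| -1.0 | 0.4 | 0.5 | 0.72 | 0.62 | 8% | 12% | 83.3% |
| -1.3 | 0.2 | 0.5 | 0.92 | 0.75 | 5% | 6% | 82.1% |
| -1.3 | 0.2 | 0.6 | 0.92 | 0.70 | 4% | 4% | 81.5% |

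Selection does not remove the gain. The power column sets 80% for the model with enrolment alone.

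**If the planning SD is unadjusted.** The protocol does not label the 0.55 to 0.82. If it is a raw SD, one baseline already turns 0.32 SD into 0.32/√(1 − r²): 0.40 at r = 0.6, 0.45 at 0.7 and 0.53 at 0.8. Power is then 93.4%, 97.3% and 99.6%. Adding the second reading with rb of 0.85 to 0.90 raises these to at most 94.4%, 98.1% and 99.9%, a gain of one point or less.

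**The case against.** The strongest reply is that nothing here is wrong. The article does not say that a single reading is used; the definition of baseline is commonly left to the full protocol or SAP; and a linear model adjusted for site and one baseline is standard. This largely stands, and it limits the point to a suggestion on efficiency.

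Several stronger readings are tempting and are not supported:

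- A reader might infer that one reading is discarded. The wording under Outcome measures is singular, but the analysis section speaks of baseline measures in the plural, and neither excludes using both.
- A reader might infer that regression to the mean in the screening value biases the result. It affects both randomised arms alike and does not bias the comparison.
- A reader might infer that power is tight and the second reading rescues it. That depends on an SD that the protocol does not identify as raw or adjusted.
- A reader might call the change free. It needs a rule for poor traces. The protocol also states neither the interval between the readings nor the bronchodilator state at the repeat, so their comparability has to be fixed.

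The timing objection also stands in part: the pre-dose order is a reasonable inference from the text, but it is not stated there. Fig. 1, whose content was not available, may settle it.

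The objection that mixing a selected with an unselected reading erodes the gain is met by the simulation: the gain persists after truncation.

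**Conclusion.** The point holds as an efficiency improvement and a clarification. Two usable pre-treatment readings appear to be collected, and the primary model does not say how they are used. In large samples, adjusting for both cannot raise residual variance and will usually lower it.

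Under the assumed values with selection at -1.0, the fall is roughly 4% to 11% against enrolment alone, or about 2 to 4 power points from an 80% base. It shrinks to about 1 to 2 points without selection when the readings correlate about 0.95 and r is 0.8 or less, and to one point or less if the planning SD is unadjusted. All of this rests on assumed correlations, on two-sided alpha of 0.05, and on the enrolment reading being taken before the first dose.

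**What to change.** State that the enrolment spirometry is completed before the first dose. Before unblinding, pre-specify that the primary model includes both pre-dose, pre-bronchodilator FEV1 z-scores (screening and enrolment) as covariates, or their mean. Where one trace is unacceptable, use the available reading. Use the same baseline for the 18-month FEV1 outcome and for the interaction with baseline severity.

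The cost is a sentence or two of wording, at most one degree of freedom in about 300, and the missing-trace rule. No new data or visits are needed.
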